#### Missing data

4.1.2

If the combined rate of missingness on a variable is less than 5%, we will not impute missing data. In the event of unanticipated higher levels of missing data, we will examine the nature of the missing values. If it is believed that variations in attrition can be explained by observed variables, these data will be considered missing at random (MAR) and no special adjustments will be necessary [70]. If, instead, we find that a portion of the variability in attrition could be explained further by unobserved variables, we will employ multiple imputation, carrying the last observation forward.

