### Overview

2.1

The currently proposed study is a community-based, pragmatic randomized-controlled trial. The aims of this study are to 1) test the impact of PlayFit, compared to Small Team Training (STT; i.e., group exercise), on cardiorespiratory fitness (i.e., VO_2peak_) and moderate-to vigorous-intensity physical activity (MVPA; self-reported and objectively monitored) after 6-and 12-months, and 2) examine group differences in rates of injury and PA program enjoyment and changes in self-efficacy, blood pressure, loneliness, anxiety, and depression. We hypothesize that participants randomized to both groups will improve their cardiorespiratory fitness similarly at month-6 (i.e., approximately 3.5 ml/kg/min), but those randomized to PlayFit will maintain these increases at month-12 through better attendance. Additionally, we hypothesize that changes in group attendance and cardiorespiratory fitness at month-12 will be mediated by group enjoyment. Finally, we hypothesize that participants randomized to PlayFit will demonstrate greater improvements in indices of physical health (i.e., blood pressure) and mental health-related (i.e., anxiety) outcomes compared to STT while reporting similar injury rates. All study procedures presented here have been approved by the Institutional Review Board (IRB).

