#### Mediators

2.4.1

All questionnaire-based measurements will be collected electronically using the Research Electronic Data Capture (REDCap [44]) system, a secure, web-based software platform.

**Physical activity enjoyment.** Participants will rate their perceived enjoyment of PA at baseline, 6, and 12-months using the Physical Activity Enjoyment Scale (PACES [45]), an 18-item questionnaire with 7-point bipolar scales where a higher score indicates greater perceived enjoyment. The stem, “Think about the exercise you have been doing…” is followed by items such as, “something I liked–something I disliked”. We will modify the stem to target specific enjoyment for the group to which the participant is assigned. (e.g., “Think about the exercise group you have been participating in during this study…"). The PACES has demonstrated excellent reliability in other adult samples [45].

**Exercise adherence.** Daily attendance logs will be maintained by the exercise leaders supervising each group.

**Self-reported physical activity.** Participants will self-report PA using the long-form of the International Physical Activity Questionnaire (IPAQ; [31]). The 31-item IPAQ was designed to provide an evaluation of PA in four domains: work, household, transportation, and leisure. A reference period of “during the last 7 days” will be used when collecting responses. The eight-day test-retest reliability for PA recall of the IPAQ was good with a median coefficient of *r* = 0.80. Criterion validity using accelerometers was acceptable with a median coefficient of 0.40 [46].

**Adverse events and injuries.** We will assess injuries and other adverse events monthly, using a self-report measure adapted from the one developed by Stathokostas and colleagues [47]. The questionnaire consists of 7-items that focus on the region of the body that is injured as well as the injury severity (i.e., whether the participant should contact or visit his or her PCP). Stathokostas and colleagues reported high test–retest reliability (*r* = 0.76) for this measure, with interrater agreement coefficients (*κ*) greater than 0.80.

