#### Preliminary data analysis plan

4.1.1

Given the relationship between cardiorespiratory fitness and mortality [69], we will conduct the primary analysis on changes in fitness. First, to ensure successful randomization, the two groups will be examined for homogeneity. If it is determined that the groups differ significantly on any variable, we will include those variables as covariates in subsequent analyses. For the primary outcome (VO_2peak_), we will apply intention-to-treat (ITT) principles with all available data included in the first set of analyses [70,71], with the assumption that participants who are lost to follow-up will not have changed their level of fitness since their last observation.

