#### Analysis of main outcome: fitness changes

4.1.3

To conduct these analyses using the principles of ITT, a slope will be fitted for the outcome variable (i.e., VO_2peak_) across each time point. Provided statistical assumptions are met, our hypotheses will be tested using random regression models [72,73]. Random regression models, also known as growth models, help to attenuate the impact of random data fluctuations, thereby increasing statistical power [72,74]. The use of random regression models also accounts for data non-independence, missing data, and nonlinear changes in the outcome variables [75].

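### The missing-data rule treats attrition explained by observed variables as needing no adjustment, but the fitness model as described omits attendance and enjoyment, so the month-12 difference may be biased toward zero; the carry-forward text conflicts with the rule.

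*Protocol article*

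**What the plan says.** The protocol article treats missing VO2peak in three places.

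- **4.1.2 Missing data.** Below 5% missing, nothing is imputed. Above that, if attrition is believed to be explained by observed variables, "these data will be considered missing at random (MAR) and no special adjustments will be necessary". If unobserved variables are found to explain part of it, "we will employ multiple imputation, carrying the last observation forward".
- **4.1.1 Preliminary data analysis plan.** The intention-to-treat analysis of VO2peak assumes that people lost to follow-up have kept the fitness level last measured. The only stated route for covariates is the check of randomization: "If it is determined that the groups differ significantly on any variable, we will include those variables as covariates in subsequent analyses".
- **4.1.3 Analysis of main outcome.** In a random regression model, "a slope will be fitted for the outcome variable (i.e., VO_2peak_) across each time point". The section adds: "The use of random regression models also accounts for data non-independence, missing data, and nonlinear changes in the outcome variables". It names no auxiliary variables.

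Attendance is central to the hypothesis. Section 2.1 expects that "those randomized to PlayFit will maintain these increases at month-12 through better attendance", and 4.1 attributes the month-12 difference to adherence. Attendance is recorded: "Daily attendance logs will be maintained by the exercise leaders supervising each group" (2.4.1). Attendance and enjoyment enter the analysis only as mediators, in the separate regressions of 4.1.5.

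**The concern.** A likelihood-based growth model is valid under MAR only given the data inside it: here VO2peak history, group and any covariates. If a variable outside the model predicts both dropout and month-12 VO2peak, an adjustment is needed. The rule in 4.1.2 prescribes no action in just the case where observed data could supply a correction.

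This matters here because the plan itself says that attendance drives month-12 fitness. It is a natural inference, though not a statement in the article, that people who stop attending are also likelier to skip the month-12 treadmill test. With poorer adherence expected in STT, the STT participants still tested at month 12 would be fitter than the arm as a whole, and the primary difference would shrink.

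The other branch offers no safeguard. Its trigger cannot be tested, because observed data cannot show that unobserved variables drive attrition. Its remedy joins two different methods, multiple imputation and carry-forward.

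**Working it through.** **1. The plan's own figure (4.1).** SD 6.0 at each time point and correlation 0.39 give a change-score SD of 6 × √(2 − 2 × 0.39) = 6.627. With 112 per group, SE = 6.627 × √(2/112) = 0.886. For a difference of 2.5, power is 80.6% by the normal approximation and 80.3% by the noncentral t. The stated 112 reproduces. 112 × 1.25 = 140 per arm, 280 in all, which allows for 1 − 224/280 = 20% attrition.

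**2. Closed form for selective loss (assumed inputs).** Suppose attenders hold a gain g at month 12 and stoppers return to 0. The stopper share p in each arm is set to reproduce the planned 3.5 and 1.0. The mean among those tested is g·a/(s + a), with s = p(1 − missing rate of stoppers) and a = (1 − p)(1 − missing rate of attenders). Power uses SE 0.886 and the normal approximation.

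| g | Stoppers, PlayFit / STT | Missing 25% / 10% (stoppers / attenders) | Missing 40% / 10% | Missing 50% / 5% |
|---|---|---|---|---|
| 3.5 | 0% / 71% | 2.36 (76%) | 2.19 (69.5%) | 1.99 (61%) |
| 4.0 | 12.5% / 75% | 2.43 (78%) | 2.32 (74.5%) | 2.17 (69%) |
| 4.5 | 22% / 78% | 2.49 (80%) | 2.43 (78%) | 2.33 (75%) |

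Example (g = 3.5, missing 40% / 10%): s = 0.714 × 0.60 = 0.429 and a = 0.286 × 0.90 = 0.257, so the STT mean is 3.5 × 0.257/0.686 = 1.31 and the difference is 3.5 − 1.31 = 2.19. Missingness is then 10% in PlayFit and 31% in STT, or 21% overall. The strongest case in that row has 5% and 37%. Simulating the two stronger cases of the first row, with imputation from baseline and month-6 VO2peak only, gave 2.17 and 1.96. There, stopping was generated independently of earlier VO2peak.

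**3. A second mechanism (simulation, 400,000 per arm).** It used the plan's means, SD 6.0 and correlation 0.39. Assumed: an attendance effect of 0 to 3 ml/kg/min per SD on month-12 VO2peak beyond earlier values, and a dropout log-odds slope of 0.5 or 1 per SD. Month-12 means were estimated by maximum likelihood given VO2peak at 0 and 6 months, by arm. Rows with an effect of 1 to 3 cover both slopes.

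| Dropout, PlayFit / STT | Attendance effect | Difference without attendance | With attendance as auxiliary |
|---|---|---|---|
| Any of the three below | 0 | about 2.5 | about 2.5 |
| 20% / 20% | 1 to 3 | about 2.5 | about 2.5 |
| 15% / 25% | 1 to 3 | 2.45 to 2.23 | about 2.5 |
| 10% / 30% | 1 to 3 | 2.39 to 2.00 | about 2.5 |

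An effect of 3 is strong. Given VO2peak at 0 and 6 months, the residual variance is 36 × (1 − 2 × 0.39²/1.39) = 28.1, and 3² = 9 is 32% of it.

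**4. The carry-forward reading.** Take people tested at month 6 (+3.5 in both arms) and lost afterwards. If loss at rate d in STT is unrelated to attendance, the STT mean becomes 3.5d + 1.0(1 − d), so the difference is 2.5(1 − d): 2.00, 1.88 and 1.75 for d = 20%, 25% and 30%. With attendance-driven loss the simulation went as low as 1.45. So this reading gives about 1.45 to 2.0, and it falls short even when dropout is equal across arms.

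**The case against.** **Condensed article.** Section 4.1.3 gives no full list of model terms, and auxiliary variables and sensitivity analyses often sit in an SAP. This stands for the detail: attendance is absent from the model as described, and no more can be said. It does not save the sentence in 4.1.2, which is a stated rule and is wrong as worded.

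**Stronger reading.** A reader might infer that the month-12 difference is biased. The documents do not support that. They name no variable as explaining attrition and give no attrition rate by arm. Bias requires attendance or enjoyment to predict dropout, to predict month-12 VO2peak beyond earlier VO2peak, and to do so with errors that differ by arm. With equal rates and mechanism it was zero. Enjoyment was not quantified at all.

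**Month-6 fitness.** A reader might also infer that VO2peak history cannot help because both arms are expected to be equal at month 6. That does not follow. The model conditions on individuals within arms, and a person's month-6 value may predict later stopping. How much it would recover is unknown.

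**Extreme split.** The largest losses come from 0% versus 71% stoppers. Allowing some stopping in PlayFit moves the estimates to about 2.2 to 2.5. This stands.

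**Remedy.** Recovery to 2.5 used the very variable that generated dropout. Real attendance counts are noisier. It is inferred, not stated, that the logs stay complete for everyone randomized. Month-12 enjoyment may be missing for the same people.

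**Direction.** The shift is toward zero. In these scenarios it costs power and does not create a false PlayFit benefit.

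**Which rule operates.** If 4.1.1 governs, the estimates under steps 2 and 3 do not describe the planned analysis, and those under step 4 do. That is a reason to settle the conflict.

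**Conclusion.** The concern holds in a limited form. The MAR rule in 4.1.2 is wrong as written, and it bears on the primary outcome of a trial whose hypothesis runs through attendance. The month-12 difference may be biased toward zero by 0 to about 0.5 of the planned 2.5 ml/kg/min, up to about 20% of the effect. Power would lie between about 80% and, in the most extreme case, about 61%. These sizes rest on assumed stopper shares, missing rates and attendance effects, and zero is within the range.

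Separately, 4.1.1 and the second branch of 4.1.2 assume no change after the last observation. That conflicts with MAR and with the plan's own expectation for STT. The text does not settle which assumption governs the primary analysis. The change should be made, preferably before month-12 data are seen.

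**What to change.** Replace the MAR sentence in 4.1.2 and the last-observation assumption in 4.1.1 with one primary rule:

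- Missing VO2peak is multiply imputed by arm from baseline and month-6 VO2peak, age, sex, logged attendance in months 1–6 and 7–12 (zero after a participant stops), and the available enjoyment and satisfaction scores.
- The month-12 comparison is then fitted without attendance or enjoyment. They are mediators measured after randomization, and adjusting for them would remove part of the effect under test.

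Replace the unobserved-variables branch with a prespecified delta-adjusted sensitivity analysis that lowers imputed month-12 values by a fixed range of amounts, separately in each arm. A range from 0 to 3.5 ml/kg/min would span loss of the whole expected month-6 gain.

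The cost is rewording two sections and some extra analysis, with no new visits or data. Recovery will be only partial if attendance is a noisy proxy for the cause of dropout, which is why the sensitivity analysis is needed.

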#### Analysis of main outcome: fitness changes

4.1.3

To conduct these analyses using the principles of ITT, a slope will be fitted for the outcome variable (i.e., VO_2peak_) across each time point. Provided statistical assumptions are met, our hypotheses will be tested using random regression models [72,73]. Random regression models, also known as growth models, help to attenuate the impact of random data fluctuations, thereby increasing statistical power [72,74]. The use of random regression models also accounts for data non-independence, missing data, and nonlinear changes in the outcome variables [75].

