#### Primary outcomes

2.3.1

**Cardiorespiratory fitness (VO**_**2peak**_**).** Cardiorespiratory fitness at baseline and month-6 and-12 will be assessed using a graded-exercise test (GXT). The GXT will be performed using a Bruce protocol [37] on a computerized treadmill while breath-by-breath data is collected using a two-way valve attached to a metabolic measurement system, such as Parvomedics (Salt Lake City, UT). Prior to each test, the system will be calibrated for oxygen and carbon dioxide using a certified mixture of the gases and for ventilation using a 3-l syringe and a standard 15-stroke calibration procedure. During each GXT, a clinical exercise physiologist will collect heart rate and blood pressure measurements, as well as monitor electrocardiography (ECG) data for adverse responses. The test will be terminated at the point of volitional exhaustion. We will consider VO_2peak_ as the point at which three or more of the following criteria are met: 1) a plateau in VO_2_ despite increasing running speed, 2) a respiratory exchange ratio (RER) higher than 1.1, 3) an inability to maintain the required velocity, or 4) heart rate above 90% of age-predicted maximum [38].

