### Sample size determination

4.1

Our power and sample size calculations are based on the following considerations. First, studies among untrained adults have shown that supervised group exercise can increase VO_2peak_ by approximately 4 ml/kg/min over 12 months [[64], [65], [66]]. Based on data derived from the National Health and Nutrition Examination Survey (NHANES) among men (*mean*_VO2peak_ = 42.1 ml/kg/minute) and women (*mean*_VO2peak_ = 34.2 ml/kg/minute) 30–39 years of age [67], we assume the baseline VO_2peak_ of participants will be approximately 35.0 (SD = 6.0). The SD of 6.0 is a conservative estimate using data from the Naval Research Lab, where it was 6.3 and 3.9 in men and women, respectively [68]. After 6-months, we anticipate that participants in both PlayFit and STT will improve their VO_2peak_ by approximately 10% (i.e., 3.5 ml/kg/min), owing to similar rates of program adherence. However, after 12-months, we anticipate only those randomized to PlayFit will maintain these changes in cardiorespiratory fitness, due to better program adherence. These differences in adherence will lead to a maintained improvement (versus baseline) in VO_2peak_ of PlayFit participants at 12-months of 3.5 ± 6.0 ml/kg/minute versus 1.0 ± 6.0 for STT. In this case, sample sizes of 112 in each group achieve 80% power to detect a mean difference of 2.5 ml/kg/minute with a standard deviation of 6.0 at the first time point, a standard deviation of 6.0 at the second time point, a two-sided significance level (*α*) of 0.05, and a correlation between measurements of 0.39. To account for participant attrition, we will oversample at a rate of 25%. Therefore, we will recruit up to 280 participants for the proposed study.

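### A single slope over 0, 6 and 12 months does not match the expected rise-then-divergence in VO2peak; read as linear, it leaves month 6 untested and can dilute the month-12 difference when participants are lost after month 6

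*Protocol article*

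**What the plan says.** Section 4.1.3 describes the main analysis in two steps: "a slope will be fitted for the outcome variable (i.e., VO_2peak_) across each time point", and then "our hypotheses will be tested using random regression models". It adds that "The use of random regression models also accounts for data non-independence, missing data, and nonlinear changes in the outcome variables". It names no quadratic, piecewise or categorical time term, and no contrast at month 6 or month 12. Section 4.1.4 plans a slope per outcome for the secondary outcomes too.

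Section 2.1 expects both arms to gain about 3.5 ml/kg/min by month 6, "but those randomized to PlayFit will maintain these increases at month-12 through better attendance". Section 4.1 puts the 12-month changes at "3.5 ± 6.0 ml/kg/minute versus 1.0 ± 6.0 for STT" and powers the trial on the difference of 2.5. VO2peak is measured at baseline, month 6 and month 12 (section 2.3.1).

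On loss to follow-up, section 4.1.1 assumes that a lost participant stays at the last measured fitness level. Section 4.1.2 makes no adjustment if data are judged missing at random, and otherwise refers to multiple imputation with the last value carried forward.

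**The concern.** The expected trajectories are a rise followed by a plateau (PlayFit) and a rise followed by a fall (STT). The arms are meant to be alike over the first six months and to part over the second six. One slope per arm averages these two phases, and the turn at month 6 is what the trial is about.

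Two things are at stake. First, the month-6 hypothesis cannot be read from a model with one linear time term. Second, a participant last seen at month 6 has shown only the early rise, which is the same in both arms. A linear model projects that rise to month 12. This pulls the arms together, and more so if STT loses more participants. Treating the data as missing at random does not cure this, because that protection needs a correct model for the mean.

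**Working it through.** **Inputs.** From section 4.1: baseline 35.0, SD 6.0, correlation 0.39, two-sided alpha 0.05, 112 per arm, 280 recruited (140 per arm), expected means PlayFit 35/38.5/38.5 and STT 35/38.5/36. Visit times are 0, 6 and 12 months (section 2.3.1). Assumed here: how dropout splits between arms and when it occurs, the within-person covariance, an intercept per arm, and dropout unrelated to outcome within an arm. The article gives only an overall attrition allowance.

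**1. The plan's own figure.**
- SD of change = 6 × √(2 × (1 − 0.39)) = 6.627.
- SE at 112 per arm = 6.627 × √(2/112) = 0.886.
- Power = Φ(2.5/0.886 − 1.96) = 80.6% (80.3% by noncentral t), so the stated 112 is reproduced.
- 224 × 1.25 = 280, and 20% loss from 280 leaves 224.

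**2. Linear slope, complete data.** The least-squares weights for slope × 12 on months 0, 6 and 12 are (−1, 0, +1), so month 6 has no weight.
- PlayFit: 38.5 − 35 = 3.5. STT: 36 − 35 = 1.0. Difference 2.5, SE 0.886, power 80.6%, the same as the powered contrast.
- Implied difference in change at month 6 = 6 × (2.5/12) = 1.25. The hypothesis is 3.5 − 3.5 = 0.
- The equality at month 12 needs an intercept per arm. With one shared baseline intercept, the fitted difference is 2.22 (constant correlation) or 2.37 (decaying correlation).

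**3. Linear slope, loss after month 6, observed data only.** For each arm the large-sample estimate is β = (Σ fₖXₖ′Vₖ⁻¹Xₖ)⁻¹ Σ fₖXₖ′Vₖ⁻¹mₖ. The sum runs over dropout patterns k with fractions fₖ. Xₖ holds the intercept and time columns, Vₖ the covariance and mₖ the expected means, each at the observed visits. With 140 per arm:

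| Loss after month 6 (PlayFit/STT) | Linear, constant r = 0.39 | Linear, decaying r (0.62 adjacent, 0.39 for 0–12) | Categorical visit |
|---|---|---|---|
| 20%/20% | 2.37, power 80% | 2.31, power 79% | 2.5, power 83% / 85% |
| 10%/30% | 2.08, power 68% | 1.87, power 61% | 2.5, power 83% / 84% |

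The last column gives power under the constant and then the decaying correlation. In the 10%/30% case with constant correlation the linear arm estimates are 3.58 and 1.50. The SE is 0.853 linear and 0.858 categorical, so the power loss comes from the smaller estimate. If the 20% per arm is instead lost before month 6, the linear difference is 2.45 (constant correlation).

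**4. Hand check of the mechanism,** using within-person information only. A three-visit participant has time sum of squares 72. A two-visit participant has 18 and a slope × 12 of 7.0 in either arm.
- 20%/20%: weights 0.8 × 72 = 57.6 and 0.2 × 18 = 3.6. PlayFit (57.6 × 3.5 + 3.6 × 7)/61.2 = 3.71; STT (57.6 × 1 + 3.6 × 7)/61.2 = 1.35; difference about 2.35.
- 10%/30%: PlayFit (64.8 × 3.5 + 1.8 × 7)/66.6 = 3.59; STT (50.4 × 1 + 5.4 × 7)/55.8 = 1.58; difference about 2.01.

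These lie close to the full estimates of 2.37 and 2.08.

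**5. If the month-6 value is carried forward instead.** The STT 12-month mean change is 0.8 × 1.0 + 0.2 × 3.5 = 1.5 at 20%/20%, and 0.7 × 1.0 + 0.3 × 3.5 = 1.75 at 10%/30%. PlayFit stays at 3.5. The differences are 2.0 and 1.75. All three values are then filled in, so slope and categorical visit give the same month-12 answer.

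**The case against.** The article never says linear. It says that growth models cope with nonlinear change, and a condensed article may leave the time form to an analysis plan. This stands in part: linear is a reading, though the natural one. The remark on nonlinearity describes what the model class can do. The only time term that the text plans is a slope, and that is stated rather than left open.

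A reader might infer that the analysis cannot test the trial's hypotheses at all. The documents do not support this. With complete data at equally spaced visits and an intercept per arm, the slope difference is the 12-month change difference, with the powered SE and power. Only the month-6 hypothesis is lost.

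A reader might also infer that dropout necessarily biases the planned result in this way. That needs three conditions: a linear form, losses, chiefly after month 6, and no carrying forward. If sections 4.1.1 and 4.1.2 are carried out by filling in the last value, nothing is extrapolated. Any shrinkage then comes from the carry-forward, and the change proposed here would not remove it.

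Finally, the 10%/30% split is an assumption. Heavier STT loss is plausible because poorer STT adherence is hypothesised, but missing sessions is not the same as leaving the study.

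**Conclusion.** The concern holds in a limited form. The single slope in sections 4.1.3 and 4.1.4 does not fit the trajectory that the plan expects. Read as linear, it provides no month-6 test and implies a difference of 1.25 ml/kg/min where the plan expects 0.

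The month-12 comparison is intact with complete data, and the sample size is sound. With observed data only, the attenuation at month 12 is modest at the plan's own 20% allowance: about 5% to 8% (2.37 or 2.31 against 2.5). It becomes material, about 17% to 25% (2.08 or 1.87), if STT loses 30% and PlayFit 10% after month 6. These sizes rest on the assumed dropout patterns and on the two assumed correlation structures. The point is worth correcting before analysis, but it does not invalidate the trial's main comparison.

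**What to change.** In sections 4.1.3 and 4.1.4, replace the single slope with visit as a categorical factor (baseline, 6, 12), group-by-visit terms and an unstructured within-person covariance. A piecewise growth model with a knot at month 6 has an equivalent mean structure and stays closer to the present wording. For VO2peak, name the PlayFit minus STT difference in baseline-to-month-12 change as the primary contrast, which is the one already powered, and report the month-6 contrast from the same model. State whether the model uses observed data only or carried-forward values, so that sections 4.1.1 to 4.1.3 describe one analysis.

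The cost is wording, one extra mean parameter per arm (three instead of two), and an SE increase of under 1% (0.858 against 0.853 in the 10%/30% case). With complete data the month-12 estimate does not change from that of a slope with an intercept per arm.
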